#### 4.2.3. Study Variables

Study variables include those related to the biopsychosocial characteristics of nursing professionals (age, sex, educational level, sexual orientation, primary care centre, employment type and years of experience in primary care) collected via an ad hoc questionnaire and the 12 items of the SABS scale (Table 1) [34].

#### 4.2.4. Procedure, Sample Size and Data Analysis

The validated Sexuality Attitudes and Beliefs Survey (SABS) [34] will be used as the measurement instrument. The sample will be divided into two groups:Group A: Nursing professionals who complete the SABS scale with a brief introduction making specific reference to the sexual and reproductive care of LGBTQ+ individuals.Group B: Nursing professionals who complete the SABS scale with a brief introduction referring to the sexual and reproductive care of the general population, without specifying sexual orientation or gender identity.

Data collection procedure:Initial contact will be made with the heads of the health centres to inform them of the study objectives and obtain institutional consent. Following acceptance, cluster allocation will be performed to generate two groups (Group A and Group B). To ensure maximum methodological rigour, the cluster allocation sequence will be generated by an independent statistical researcher who is completely external to data collection and recruitment. The generation will be performed using a computerized random number generator. Allocation concealment will be maintained at the institutional level: health centres will be assigned to either Group A or Group B simultaneously, and participating nurses will be blinded to the existence of an alternative version of the survey, mitigating potential performance or social desirability biases.The SABS scale will be used to evaluate attitudes and beliefs around human sexuality in nursing, with the aim of detecting obstacles in sexual counselling and recommendations.

The complete survey comprised: (1) an ad hoc section collecting sociodemographic data (age, primary care centre, nationality, sex, sexual orientation, educational level, employment type, and years of experience in primary care), and (2) 12 SABS items rated on a five-point Likert scale (1 = Strongly disagree to 5 = Strongly agree). The survey will be distributed electronically via the LimeSurvey platform, with biweekly reminders to maximize response rates.

#### 4.2.5. Statistical Analysis

Statistical analysis will be conducted using open-source software Jamovi version 2.12.0 (The jamovi project, Sydney, Australia). The analytical process will be structured as follows:

Descriptive and exploratory analysis.

Categorical (nominal) variables are expressed as absolute and relative frequencies (percentages). For ordinal variables (Likert items) and non-normally distributed quantitative variables, non-parametric measures of central tendency and dispersion use median (Mdn), interquartile range (IQR), and minimum/maximum values.

Inferential analysis and hypothesis testing.

After verifying non-compliance with normality assumptions (Shapiro–Wilk test), non-parametric tests will be applied:Pearson Chi-square (χ^2^) for associations between categorical variables.Mann–Whitney U for two-group median comparisons.Kruskal–Wallis H for comparisons involving more than two groups.

Robustness and variability control.

Homogeneity of variances will be assessed using Levene’s test. Where heteroscedasticity is detected, appropriate robust adjustments will be applied. A 95% confidence level and statistical significance threshold of *p* < 0.05 will be set for all analyses.

Regarding the management of missing data, the mechanism of missingness will be evaluated using Little’s Missing Completely at Random (MCAR) test; if missing data exceed 5%, Multiple Imputation by Chained Equations (MICE) will be applied. To quantify the magnitude of the differences, appropriate non-parametric effect sizes will be calculated and reported: Rank-biserial correlation for Mann–Whitney U tests and epsilon-squared for Kruskal–Wallis tests. The internal consistency of the SABS instrument within our specific study sample will be rigorously assessed by calculating both Cronbach’s alpha and McDonald’s omega coefficients. Finally, to control the type I error rate during multiple comparisons, *p*-values will be adjusted using the Benjamini–Hochberg False-Discovery Rate (FDR) procedure where appropriate.

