#### 4.2.2. Study Sample and Inclusion/Exclusion Criteria

Given the exploratory nature of this phase, the study is configured as a pilot and feasibility study. A total sample of *n* = 112 subjects is gathered via cluster allocation at the health-centre level. To justify the statistical validity of this sample size under a cluster design perspective, we consider a total of 33 health centres (clusters) with an estimated average cluster size of m approx 3.4 nurses. Assuming a conservative Intraclass Correlation Coefficient (ICC) of *p* = 0.02 for attitudinal measurements in primary care, the calculated Design Effect (Deff) is approximately 1.05 [Deff = 1 + (m − 1)*p*]. This indicates that the variance inflation due to clustering is minimal, confirming that the sample size of *n* = 112 retains sufficient statistical power for this pilot exploration while matching formal feasibility criteria.

Inclusion criteria: Nursing professionals currently working in primary care within the MVGHD who freely accept participation as indicated by the integrated informed consent within the survey.Exclusion criteria: Healthcare professionals performing functions outside the scope of community nursing or working in settings other than primary care.

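### Whole health centres are allocated to questionnaire version A or B, but the planned two-group score test treats the 112 nurses as independent, so A-versus-B p-values are too small if nurses within a centre are correlated

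*Protocol article*

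**What the plan says.** Section 4.2.4 makes the centre the unit of allocation: "health centres will be assigned to either Group A or Group B simultaneously", from a computer-generated random sequence, after the heads of centres have agreed. Section 4.2.2 describes a sample of 112 "subjects is gathered via cluster allocation at the health-centre level" and counts "33 health centres (clusters) with an estimated average cluster size of m approx 3.4 nurses". It sets the within-centre correlation with the words "Assuming a conservative Intraclass Correlation Coefficient (ICC) of" 0.02, so that "the calculated Design Effect (Deff) is approximately 1.05", and concludes: "This indicates that the variance inflation due to clustering is minimal".

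Section 4.2.5 lists three tests: Pearson chi-square, "Mann–Whitney U for two-group median comparisons", and Kruskal–Wallis for more than two groups. The effect sizes are "Rank-biserial correlation for Mann–Whitney U tests and epsilon-squared for Kruskal–Wallis tests". Significance is set at 0.05 with Benjamini–Hochberg adjustment where appropriate. The only robust adjustment mentioned is for unequal variances. There is no random centre effect, clustered rank test, cluster-robust variance or centre-level summary. Centre is recorded (Sections 4.2.3 and 4.2.4, Table 1) but has no role in the analysis.

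**The concern.** Section 3 makes the overall goal a comparison between care framed around LGBTQ+ people and care framed around the general population. Section 3.1.1 makes SABS total and dimensional scores the primary outcome. Group A versus Group B is the two-group contrast that answers this question, and the Mann–Whitney U is the only two-group score test named.

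That contrast lies wholly between centres, because every nurse in a centre receives the same version. Whatever nurses in a centre share (local training, leadership, patient mix) enters the variance of the contrast in full. The usual Mann–Whitney null distribution leaves it out, so the reference variance is too small and false positives exceed the nominal rate.

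Clustering is thus allowed for when the sample size is justified and dropped when the data are tested. The reassurance in Section 4.2.2 rests on an assumed ICC that the planned analysis would never estimate.

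**Working it through.** **Inputs from the protocol.** n = 112, 33 centres, m about 3.4 (112/33 = 3.39), ICC 0.02 and design effect about 1.05 (Section 4.2.2); significance level 0.05 (Section 4.2.5). Sidedness is not stated, so two-sided is assumed.

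**Assumptions for the range.** ICCs of 0.05, 0.10 and 0.20, uneven centre sizes, and a split of 16 against 17 centres. None of these is in the protocol.

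**Step 1: reproduce the plan's figure.** Deff = 1 + (m − 1) × ICC = 1 + 2.4 × 0.02 = 1.048, which agrees with the stated 1.05. Effective sample size = 112/1.048 = 106.9.

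**Step 2: true error of a test that ignores centre.** Type I error = 2 × [1 − Φ(1.96/√Deff)]. With Deff = 1.048, √Deff = 1.024 and 1.96/1.024 = 1.914, giving 0.0555.

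**Step 3: range and simulation.** The nurse-level Mann–Whitney U was simulated under no A-versus-B difference, with 8,000 studies per setting. Near-equal sizes were 13 centres of four nurses and 20 of three. Uneven sizes were one nurse per centre, with the other 79 spread by random weights (coefficient of variation 0.8). For comparison, a t-test was run on the 33 centre means.

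| ICC | Deff (equal sizes) | Formula | Mann–Whitney, near-equal | Mann–Whitney, uneven | Centre means, near-equal / uneven |
|---|---|---|---|---|---|
| 0 | 1.000 | 5.0% | 5.2% | 5.0% | 5.3% / 5.0% |
| 0.02 (protocol) | 1.048 | 5.55% | 5.8% | 5.5% | 5.2% / 4.4% |
| 0.05 (assumed) | 1.120 | 6.4% | 5.9% | 7.6% | 4.8% / 4.9% |
| 0.10 (assumed) | 1.240 | 7.8% | 7.7% | 9.5% | 5.1% / 5.3% |
| 0.20 (assumed) | 1.480 | 10.7% | 10.5% | 14.1% | 4.8% / 5.0% |

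The simulation standard error near 5% is √(0.05 × 0.95/8000) = 0.24 percentage points. At ICC 0.02 the excess is therefore barely distinguishable from simulation noise. At 0.10 and above it is plain. The test on centre means stayed between 4.4% and 5.3% throughout.

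**Step 4: fewer centres.** Allocation follows acceptance by centre heads, so fewer than 33 may take part. As an illustration, 20 centres supplying 112 nurses give m = 5.6. Deff is then 1 + 4.6 × ICC = 1.09, 1.23 and 1.46 at ICC 0.02, 0.05 and 0.10, and the formula gives about 6%, 8% and 10%.

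**The case against.** The strongest reply is that the effect is negligible on the protocol's own numbers: about half a percentage point of extra type I error, in a study described as pilot and exploratory. That stands as to size, and it is why this is not a critical defect. It does not settle the matter. The 0.02 is called conservative without supporting data in the text, the design-effect formula uses only the average centre size, and nothing planned would reveal a higher value. If the ICC really is small, respecting centre costs almost nothing. Pilot status lowers the stakes, but the plan still tests hypotheses at 0.05. The Benjamini–Hochberg procedure takes its input p-values as valid and cannot correct ones that are too small.

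Nor can the point be left to an unseen analysis plan. The article itself names the tests, and the objection is to that stated choice.

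A reader might infer more than the protocol supports:

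- **That effect-size intervals are too narrow.** Section 4.2.5 sets a general 95% confidence level but does not expressly plan an interval for the rank-biserial correlation. Ignoring centre does not bias the effect-size estimate. Only a precision attached to it would be overstated, by about 2% of interval width at ICC 0.02 (1/√1.048 = 0.977).
- **That every test in Section 4.2.5 carries this penalty.** The figures above are for A versus B. Age, experience and education vary within centres, so the same inflation does not automatically apply to tests on them.
- **That calling the Mann–Whitney a comparison of medians adds to the case.** That is a separate wording matter and has no bearing on clustering.
- **That a linear mixed model is the one right replacement.** The plan is deliberately non-parametric, and several methods respect centre. With a true ICC of 0.02 and centres this small, a simulated analysis-of-variance ICC estimate was zero or negative in about 44% of runs. A random-intercept model would then largely reduce to the unadjusted analysis.

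**Conclusion.** Wrong as written, and it should be fixed. The A-versus-B test does not match the allocation by centre or the clustering allowance in Section 4.2.2. The direction is certain for any positive ICC. The size is not: true type I error is about 5.5% at the protocol's ICC of 0.02, and about 6% to 14% over ICCs of 0.05 to 0.20 with even to uneven centre sizes. Everything beyond the first figure rests on ICC and size assumptions that the protocol neither supports nor rules out. The protocol therefore does not show that the primary result would be seriously misleading. It shows that the p-value would not be protected if the ICC were higher than assumed.

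**What to change.** In Section 4.2.5, replace the nurse-level Mann–Whitney U for A versus B with an analysis that respects centre, chosen by the authors and fixed before data collection. Suitable options are:

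- a rank-sum permutation test that re-allocates whole centres, which keeps the non-parametric approach;
- a clustered rank-sum test;
- a comparison of centre-level summaries;
- a mixed model with a random centre intercept and a small-sample correction.

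Any interval reported for the A-versus-B effect should account for centre. Report the observed ICC with its interval, which will be wide, and do not use a low or zero estimate as grounds for dropping the adjustment. The unadjusted rank test can stay as descriptive.

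The cost is a revised paragraph, a little more analysis work, a check that the software named in Section 4.2.5 offers the chosen method, and a slightly larger p-value or wider interval. Centre is already recorded, and the Data Availability statement says data collection has yet to begin, so the change can still be prespecified.

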### 4.3. Phase II: Qualitative Descriptive Study of Discourse

#### 4.3.1. Qualitative Study Design and Participants

A second qualitative phase based on discourse analysis (DA) is proposed. This approach will explore structures of thought, interpretive repertoires, symbolic resistances and attitudinal barriers in LGBTQ+ care as expressed in the professional narratives of primary care nursing staff. The central objective is to deepen understanding of the discourses, meanings and underlying biases that could not be captured by the SABS scale due to the social desirability bias detected in Phase I.

#### 4.3.2. Study Population and Sample

An intentional sample will be selected through maximum-variation purposive sampling, seeking to represent the diversity of profiles within the MVGHD, including professionals with different years of experience, educational levels, and health centres. Based on the previous literature using discourse analysis (DA) in health service research, it is estimated that between 15 and 20 in-depth interviews will be required to achieve theoretical saturation, defined as the operational point at which new data yield no additional conceptual categories or interpretive repertoires.

#### 4.3.3. Procedure

In-depth semi-structured interviews will be used as the primary data collection technique. The interviews will be conducted by members of the research team who possess specific postgraduate qualifications and formal academic experience in qualitative health research and gender/LGBTQ+ perspective studies (specifically authors [name], [name]). A formalized, pre-tested interview protocol and semi-structured question guide will guide the process, ensuring consistency across participants while allowing space for emerging themes. The primary language utilized during the interviews will be Spanish, given the professional setting within the Andalusian Health Service; however, bilingual protocols (Spanish/English) will be available to accommodate potential diversity among participating healthcare professionals. As an optimization strategy to guarantee the authenticity of discourse and mitigate social desirability, the possibility of integrating clinical vignette elicitation will be considered, which involves presenting hypothetical scenarios to facilitate the projection of real attitudes.

#### 4.3.4. Data Analysis

Qualitative data will be analyzed via discourse analysis (DA) supported by ATLAS.ti 23 (ATLAS.ti Scientific Software Development GmbH, Berlín, Germany). The process will be structured in the following operational phases:Phase 1—Preparation and Transcription: Recorded interviews will be transcribed verbatim, preserving expressions, pauses and idioms. After a familiarization reading (data immersion), texts will be imported into ATLAS.ti 23 as “Primary Documents”.Phase 2—Open Coding (Textual Level): Inductive line-by-line coding will be performed, identifying units of meaning and assigning open codes (conceptual and in vivo). The goal is to break down discourse into its most basic components: perceived barriers, fears, beliefs and interpretive repertoires.Phase 3—Axial Coding and Categorisation (Conceptual Level): Resulting codes will be compared and grouped by semantic similarity to generate categories and subcategories. The ATLAS.ti 23 “Network View” (Semantic Networks) tool will be used to establish logical relationships between categories, enabling visualization of professional thought structures and potential heteronormativity biases.Phase 4—Integration and Triangulation (Theoretical Level): Methodological triangulation will be performed by contrasting the discourse analysis findings with the quantitative results of Phase I (SABS). Co-occurrence reports will help explain why professionals scoring high in “competence” in questionnaires manifest “terminological insecurity” or “avoidance” in their actual discourse.

Methodological Rigour and Trustworthiness: To minimize subjectivity and potential researcher bias, the qualitative phase will strictly adhere to Lincoln and Guba’s criteria for establishing trustworthiness. Credibility and confirmability will be ensured through investigator triangulation (independent open and axial coding by two separate researchers with consensus meetings) and the maintenance of a detailed reflexive research journal to track potential assumptions. Dependability will be supported by an explicit audit trail of all analytical steps within ATLAS.ti 23. Finally, member-checking will be performed by sharing verbatim summaries with a subset of participants to validate that the interpretations accurately reflect their narratives.

## 5. Discussion

This study protocol describes a sequential explanatory mixed-methods design aimed at exploring the barriers, facilitators, and competencies associated with the provision of sexual and reproductive healthcare for LGBTQ+ individuals within primary healthcare settings.

Previous research has highlighted the existence of healthcare inequalities affecting LGBTQ+ populations, including barriers related to stigma, discrimination, insufficient professional training, and limited access to culturally competent care [10,20,38,39]. Although nurses play a central role in promoting health equity and delivering person-centred care, several studies have reported gaps in knowledge, confidence, and preparedness when addressing the specific sexual and reproductive health needs of LGBTQ+ individuals [17,20,32]. Among the barriers they face is the lack of training on the specific health needs of the LGBTQ+ community, a shortcoming that generates insecurity and lack of confidence in the care provided. Moreover, the stereotypes, stigmas and prejudices related to sexual and gender diversity can have an unfavourable impact on the nurse–patient relationship, making it difficult for the parties to communicate effectively and for the patients’ reproductive needs to be properly diagnosed [10,38,39].

The quantitative phase of the present study is expected to provide preliminary evidence regarding nursing professionals’ attitudes, beliefs and perceived competencies in this area. In addition, the comparison between questionnaires framed around LGBTQ+ healthcare and those referring to the general population may help identify potential differences in professional responses that could otherwise remain unnoticed.

The qualitative phase has been designed to complement and expand these findings by exploring the meanings, experiences and interpretative frameworks underlying professional practice. Through discourse analysis, the study seeks to identify potential symbolic barriers, implicit assumptions, and contextual factors that may influence the provision of sexual and reproductive healthcare [20,30,38,39]. The proposed research is expected to emphasize that creating a discrimination-free work environment and providing ongoing training for healthcare professionals would foster inclusive, high-quality care.

One of the main strengths of this protocol lies in its mixed-methods design, which enables the integration of quantitative and qualitative evidence. This approach may facilitate a more comprehensive understanding of a complex phenomenon that cannot be fully captured through survey-based methods alone. Furthermore, the use of methodological triangulation is expected to strengthen the validity and interpretability of the findings.

Another strength is the focus on primary healthcare nurses, who often represent the first point of contact within the healthcare system and therefore play a critical role in promoting inclusive and equitable care. Understanding their perceptions and experiences may contribute to the development of targeted educational initiatives and institutional strategies aimed at improving healthcare delivery for LGBTQ+ populations.

Several limitations should also be acknowledged. For example, self-reported measures are inherently susceptible to social desirability bias, particularly when addressing sensitive topics related to sexuality and gender diversity. To mitigate this limitation, the qualitative phase will explore underlying discourses and attitudes that may not emerge through structured questionnaires.

Overall, this study is expected to contribute to the growing body of evidence concerning sexual and reproductive healthcare for LGBTQ+ populations. By identifying barriers, facilitators, and training needs among primary healthcare nurses, the findings may inform future educational programmes, organizational policies, and healthcare interventions aimed at promoting equity, inclusion, and high-quality care for sexually and gender-diverse populations [10,20].

## 6. Conclusions

This study protocol outlines a necessary framework to identify and dissect institutional discrimination towards LGBTQ+ patients within the primary healthcare system. By thoroughly analyzing both the barriers and facilitators in nursing care, this research aims to expose the systemic gaps that compromise equity and quality in healthcare delivery for sexual and gender minorities. The anticipated findings are expected to underscore a critical, undeniable need: the implementation of specialized training programmes in sexual and reproductive health tailored for nursing professionals. Addressing this educational deficit is a vital step toward dismantling institutional biases and fostering culturally competent care. Furthermore, the strategic dissemination of the results—through high-impact journals, open-access repositories, and direct communication with participating primary care centres—will not only guarantee transparency but also establish a robust, empirical foundation to guide future research, healthcare policies, and intervention strategies in LGBTQ+ health equity.

